## Data collection and management

### Plans for assessment and collection of outcomes {18a}

The study will be monitored to ensure that it is conducted in conformance with the monitoring plan to assess continued compliance with the protocol, recognized Good Clinical Practices, and US federal regulations outlined in 21 CFR Part 312. In addition, the monitor will verify that study records are adequately maintained; that data are reported in a satisfactory manner with respect to timeliness, adequacy, and accuracy; and that the investigator continues to have sufficient staff and facilities to conduct the study safely and effectively.

The study may also be participant to a quality-assurance audit by the sponsor or its designees as well as inspection by appropriate regulatory authorities. In addition to ensuring adequate communication between the investigators and the sponsor, the monitor’s duties include on-site and remote visits (as necessary) and review of study documents and reported data. The sponsor representatives will be provided with appropriate product and protocol training prior to the study and will follow a monitoring plan for all study-related monitoring activities.

On-site and remote monitoring visits will include a pre-study site initiation visit, periodic interim monitoring visits, and a close-out visit at the end of the site’s participation in the study.

Monitoring visits will be documented on monitoring visit reports and will aim to verify that:Compliance with the clinical protocol and applicable regulations is being maintained.Source data are verified and signed off upon as accurate.Participant files are accurate and complete.Participant withdrawal has been documented (if applicable).Participant non-compliance has been documented (if applicable).The investigator and site staff are informed and knowledgeable of all relevant document updates concerning the clinical investigation.Only authorized individuals are performing study-related functions.The IP is being used according to the protocol and instructions for use.Staffing and facilities are adequate.Signed and dated ICFs have been obtained from each participant.CRFs and queries are complete.All AEs are reported to the sponsor.All SAEs and unanticipated adverse events (UAEs) are reported to the sponsor and the IRB.All other required IRB reports, notifications, applications, submissions, and correspondence are maintained in the investigator’s files and are accurate.Corrective and preventive actions have been implemented (if applicable).

To ensure that the study is conducted in accordance with the terms of the clinical protocol, study monitors must visit each study site at routine intervals throughout the duration of the study. The exact frequency of visits shall be determined on an individual study site basis as detailed in the clinical monitoring plan and shall depend upon the following factors:Rate of participant enrollmentExperience of the investigator in conducting clinical studiesRecord of previous site compliance

eCRFs will be completed in a 21 CFR Part 11-compliant EDC system for each participant consented into the clinical study. The study coordinator will enter the source data onto the CRF, and it will then be entered into the EDC and study monitors will verify that the source documents match the data entered on the CRF and in the EDC. Once verified, the study monitor will lock the field or page via a monitoring approval step so the data cannot be changed unless requested.

CRFs will be completed on paper forms for each participant consented for the clinical study. The study coordinator will enter the source data onto the CRFs, and data from the CRF pages will be entered into the EDC system. Study monitors will verify that the source documents match the CRFs at selected time intervals.

All procedures for the handling and analysis of data will be conducted using good clinical data management practices within systems meeting US Food and Drug Administration (FDA) guidelines for the handling, storage, and analysis of data for clinical studies.

The investigator will sign off on the eligibility criteria, all adverse event, protocol deviation, and study completion CRFs and will sign each participant’s casebook once the participant completes the study to attest that all data entered on the CRFs are complete and accurate.

Any required data clarifications will be handled within the EDC system’s query management system. The requests will include but not be limited to queries on missing values and values out of acceptable ranges. Study coordinators will have the opportunity to correct data and/or respond to the query for review by monitors and data managers.

PROMs will be collected via paper forms and the data will be transmitted into the EDC. Any data that are originated on paper are to be considered source documentation for the purposes of this study. The data quality control measures for PROM data entry will include double data entry and automated checks in the EDC system, to minimize transcription errors.

Each participant will be identified in the database by a unique participant identifier assigned in EDC. To ensure the quality of clinical data across all participants and sites, a clinical data management review will be performed on participant data according to specifications outlined in the data management plan. Data will be vetted both electronically and manually. Queries generated and raised by reviewers will be generated within the EDC application. During this review, participant data will be checked for consistency, omissions, and any apparent discrepancies.

All AEs will be coded using the medical dictionary for regulatory activities (MedDRA), and all concomitant medication will be coded using the World Health Organization Drug Reference (WHODRUG Global) List*.*

### Plans to promote participant retention and complete follow-up {18b}

The participants will receive extensive information about the study methods, setup, and requirements during the recruitment phase. The importance of completion of the follow-up assessments will be emphasized. Patients will be allowed to withdraw from study participation at any time during the study and are not obliged to give a reason for discontinuation. All participants will be reminded throughout the study to fill out the PROMs during study visits. Throughout the follow-up period, the researchers will check responses and if necessary, contact patients for completion of their follow-up.

### Data management {19}

Each participant will be identified in the database by a unique participant identifier assigned in EDC. To ensure the quality of clinical data across all participants and sites, a clinical data management review will be performed on participant data according to specifications outlined in the data management plan. Data will be vetted both electronically and manually. Queries generated and raised by reviewers will be generated within the EDC application. During this review, participant data will be checked for consistency, omissions, and any apparent discrepancies.

### Confidentiality {27}

The investigators and the sponsor will preserve the confidentiality of all participants taking part in the study, in accordance with GCP and local regulations. The investigator will ensure that the participant’s anonymity is maintained. CRFs or other documents submitted to the sponsor will identify each participant by a unique participant identifier as designated by the sponsor. Documents that are not for submission to the sponsor (e.g., signed ICF) will be kept in strict confidence by the investigator.

In compliance with federal regulations/ICH GCP guidelines, it is required that the investigator and institution permit authorized representatives of the company, of the regulatory agency(s), and the IRB direct access to review the participant’s original medical records for verification of study-related procedures and data. The investigator is obligated to inform the participant that his/her study-related records will be reviewed by the above-named representatives without violating the confidentiality of the participant.

### Plans for collection, laboratory evaluation, and storage of biological specimens for genetic or molecular analysis in this trial/future use {33}

No biological specimens will be collected in this trial.

## Statistical methods

### Statistical methods for primary and secondary outcomes {20a}

Descriptive analyses will be performed to characterize the treatment groups and to assess equality produced in reality from the randomization to understand if no clinically significant group differences at baseline exist. Baseline variables will be compared between groups using means, standard deviations, median, minimum, and maximum values for continuous variables and count and percentages for categorical variables.

Although the emphasis will be on clinical significance, baseline comparisons will include *t*-tests or Wilcoxon rank-sum tests as appropriate for interval variables and chi-square or Fisher’s exact tests as appropriate for nominal variables to aid in the screening for baseline differences.

Changes in clinical endpoints over time will be summarized within each treatment group using summary statistics, including mean and median change scores, standard deviations, and ranges. Pearson or Spearman rank correlation coefficients will be used to characterize associations among variables within the treatment groups. For time-to-event outcomes (i.e., event-free survival), descriptive analyses will include the construction of group-specific Kaplan–Meier survival curves as appropriate. Longitudinal clinical status will be evaluated for all PROMs.

The analysis populations for this study will include the intent-to-treat (ITT) analysis set, modified intent-to-treat (MITT) analysis set, safety analysis (SA) set, and per protocol (PP) analysis set.

The primary efficacy measurements will be characterized descriptively in terms of the proportion of participants meeting at least a 30% pain improvement from baseline in VAS back-pain severity score at 12 months, in the VIA Disc NP group compared to that in the sham control group.

The claim of superiority, for the primary endpoint of month 12 VAS 30% improvement, will be accepted if the posterior probability of superiority is greater than or equal to 0.975. That is, superiority will be claimed if:

$$\mathrm{PR}(\mathrm{pT}-\mathrm{pC}>0\ |\ \mathrm{Data}) \geq 0.975$$

This posterior probability is calculated using beta non-informative Jeffreys priors for both groups. Participants who receive alternative treatments during the study, e.g., epidurals or increased narcotics, will be handled analytically in the primary endpoint calculation. In the same fashion, participants who do not complete the study will be categorized by the reason for missingness and handled according to this designation. These events (additional treatments or exiting the study for specific reasons) are called intercurrent events. At a high level, participants with temporally proximate, clinically meaningful alternative treatments will have their month 12 endpoint data imputed from participants without additional treatment. This is consistent with ICH E9R1 discussion and the methodology of defining estimates of interest and intercurrent events.

For the VAS, ODI, EuroQol (EQ-5D), and patient global impression of change (PGIC) endpoints, mean change in scores at each follow-up time-analysis will be performed with the hypothesis:

H0: dt − dc ≤ 0.

Ha: dt − dc > 0.

where “dpt” is the mean change in VAS and ODI scores among the treatment (dt) and control (dc) arms, respectively. Endpoints defined as proportions will be tested by comparing differences in proportions. The tests will be conducted with the hypotheses at each follow-up interval:

H0: pt − pc ≤ 0.

Ha: pt − pc > 0.

where “pt” and “pc” are the percentage of responders in the treatment (pt) and control arms (pc), respectively, at 12 months. These analyses will be conducted for all differences in proportion endpoints including:Proportion of participants who achieve at least a 50%-reduction in VAS score for back-pain severity SCB assessed at each follow-up intervalProportion of participants who achieve a PASS, defined as a VAS score for pain severity of 30 mm or less, assessed at each follow-up intervalProportion of participants who achieve a MCID, defined as a 30% or greater improvement in ODI score assessed at each follow-up intervalProportion of participants who achieve SCB, defined as a 50% or greater improvement in ODI score assessed at each follow-up intervalProportion of participants who achieve a PASS, defined as a ODI score for back function of 20 or less at all follow-up intervalsProportion of participants in each ODI functional impairment category assessed at each follow-up interval

Secondary endpoints will be tested using both Bayesian and frequentist statistics.

For participants that have consented to opioid use assessment via PDMP:oReductions in opioid use, defined as a ≥ 30% decrease in total dispensed MME from baseline to all follow-up intervals

A cumulative proportion of responders analysis (CPRA) will be used to robustly compare the proportion of responders achieving clinical success in ODI and VAS endpoints. Group-specific vectors of month 12 change from baseline scores will be generated. Those vectors represent group-specific cumulative proportions of responders and will be statistically compared using a 2-sample Kolmogorov–Smirnov test. The CPRA will be visualized as follows:X-axis details the point change from baseline in the PRO score at month 12.The Y-axis details the group-specific percentage of subjects achieving the corresponding x-axis’s value, 0 to 100%, where each group will start in the upper left-hand of the graphic depicting 100% of participants.

The groups include the VIA Disc NP treatment arm in blue and the control arm in red at every group-specific unique change from baseline, represented by a dot, along the group-specific distribution function.

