### Trial design {8}

This is a randomized, double-blind, sham-controlled, multi-center clinical trial with an adaptive design and a planned enrollment of up to 446 participants, including up to 21 participants in an initial non-randomized roll-in phase. Eligible participants are randomized in a 2:1 ratio via permuted block design to receive either VIA Disc NP or sham procedure. Randomization is stratified by site and previous intradiscal biological treatment (Y/N). All participants, clinical personnel, and outcome assessors are blinded to group assignment.

The primary efficacy analysis of this superiority trial will be conducted at 12 months, with long-term efficacy, safety, and exploratory imaging data collected through 24 months. Pre-specified interim analyses will be used to guide the adaptive design while controlling type 1 error inflation and power.

Sham participants who meet crossover criteria at 12 months (visual analog scale (VAS) ≥ 40 mm and ODI ≥ 40) are eligible to receive VIA Disc NP and initiate a secondary 12-month follow-up. All procedures are standardized across sites and performed under moderate conscious sedation using a fluoroscopy-guided technique.

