## Methods: participants, interventions, and outcomes

### Study setting {9}

The trial is conducted at up to 21 investigational sites across the USA, including academic and private clinical research centers with dedicated interventional spine capabilities. All sites must demonstrate operational readiness and procedural consistency during a roll-in phase prior to randomization. Investigators are board-certified or fellowship-trained in pain management, spine intervention, or a related specialty, and must be proficient in the administration of VIA Disc NP per the manufacturer’s instructions for use (IFU). Each site maintains the capacity for longitudinal follow-up and secure data management in accordance with good clinical practice (GCP) and Institutional Review Board (IRB) standards.

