### Sample size {14}

The sample size for this study is based on a sham success rate assumption of 40% and varying superiority assumptions (delta) from 12.5 to 30 percentage points [17]. For initial study planning purposes, a frequentist *Z*-test for two proportions framework with pooled variance was used to calculate the required sample size to achieve 85% power using a one-sided alpha = 0.025 and 2:1 randomization.

Table 2 shows that when VIA Disc NP performance is 20 percentage points better than sham, *N* = 248 subjects are needed before loss to follow-up (LTFU). When VIA Disc NP performance is 15 percentage points better than sham, *N* = 446 subjects are needed (before LTFU). These sample sizes (*N* = 248 and *N* = 446) are the minimum and maximum number of subjects that will be enrolled (before LTFU).

**Table 2 Tab2:** Range of sample size estimates based on MCID responder rate differences

Sham	Treatment	Delta	*N* (no LTFU)	*N* w/LTFU
40.0%	70.0%	+ 30.0%	107	119
40.0%	60.0%	+ 20.0%	248	276
40.0%	57.5%	+ 17.5%	326	362
40.0%	55.0%	+ 15.0%	446	496
40.0%	52.5%	+ 12.5%	641	712

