## Assignment of interventions: allocation

### Sequence generation {16a}

Participants in the randomization stage will be randomized to the VIA Disc NP group or the sham control group in a 2:1 ratio via permuted block randomization with randomization stratified by clinical site and previous intradiscal biological treatment (Y/N). The randomization allocation schedule will be prepared in advance by an independent statistician not involved in the conduct of the trial. The randomization schedule will be generated using a validated randomization software (e.g., SAS, R, or another secure randomization tool).

Randomization will occur at the time of the day 0 visit after all eligibility criteria have been evaluated and the ICF is signed. Randomization may be performed using the appropriate module in the electronic data capture (EDC) system.

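### The primary beta-Jeffreys comparison uses neither randomisation stratification factor nor baseline VAS: it is valid, but less precise than it could be if these are prognostic

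*Protocol article*

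**What the plan says.** Trial design {8} states: "Randomization is stratified by site and previous intradiscal biological treatment (Y/N"). Sequence generation {16a} names the same two factors. Study setting {9} allows "up to 21 investigational sites across the USA" (Recruitment {15} says 20).

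Statistical methods {20a} fixes the primary decision. Superiority on the 12-month 30% VAS responder endpoint is claimed if "the posterior probability of superiority is greater than or equal to 0.975". On the model it says: "This posterior probability is calculated using beta non-informative Jeffreys priors for both groups". No adjusted primary or supporting analysis is named.

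The only model covariates in the statistical sections are in {20c}: age, sex, body mass index and race/ethnicity. They are optional, serve only the imputation of missing month-12 data, and do not include the stratification factors or baseline VAS.

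Sample size {14} plans with a "frequentist *Z*-test for two proportions framework with pooled variance", "to achieve 85% power using a one-sided alpha = 0.025 and 2:1 randomization".

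**The concern.** A separate beta posterior for each arm is a two-rate model. If responder rates differ between sites, or by prior biological treatment, stratified randomisation makes the arms more alike on those factors than simple randomisation would. An analysis that ignores them still counts that variation as noise, so the posterior for pT − pC is wider than the design warrants.

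Baseline VAS is a different case. It is not a stratification factor, so the design does not balance it. It is measured on everyone, ranges from 40 to 90 mm at entry and is the denominator of the endpoint. If it predicts response, adjusting for it would also reduce variance and remove the effect of chance imbalance.

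What is at stake is efficiency, not validity. It matters somewhat more here because the maximum sample size leaves little room at the smallest effect for which the trial is sized.

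**Working it through.** **Inputs from the protocol article.** Sham rate 40%, treatment rate 55% at the maximum N of 446, one-sided alpha 0.025, 85% power, 2:1 allocation ({14}). Up to 21 non-randomised roll-ins are counted within the 446 ({8}). The loss rate is not stated, but Table 2 implies 10%: 248/0.9 = 276 and 446/0.9 = 496.

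**Assumption.** The share of outcome variance (R²) explained by site, prior biological treatment and baseline VAS together is not given. It is varied below from 0 to 10%.

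**1. Reproduce the plan's figure.** With a 2:1 split the pooled rate is (0.40 + 2 × 0.55)/3 = 0.50.

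N = 3 × [1.960 × √(0.25 × 1.5) + 1.036 × √(0.24 + 0.2475/2)]² / 0.15²
= 3 × (1.200 + 0.625)² / 0.0225 ≈ 444.2

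Rounding up per arm gives 447, against 446 stated. The other rows of Table 2 also agree to within 1.

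**2. Check the stated Jeffreys rule as written.** Exact binomial enumeration, single look, null rate 40%:

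| Treatment/sham | Type I error | Power, 55% vs 40% | Power, 60% vs 40% |
|---|---|---|---|
| 297/149 (446) | 0.0250 | 85.6% | 98.1% |
| 283/142 (425) | 0.0253 | 83.0% | 97.5% |
| 255/128 (383) | 0.0249 | 79.8% | 96.2% |

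The unadjusted rule therefore delivers the planned 85% at 446.

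**3. Evaluable number.** 446 − 21 = 425 randomised; 425 × 0.9 = 382.5. With 382.5/3 = 127.5 sham participants, pooled-Z power is

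Φ[(0.15 × √127.5 − 1.200)/0.603] = Φ(0.818) = 79.3%

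**4. Value of adjustment.** Linear approximation, effective N = 382.5/(1 − R²):

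| R² (assumed) | Effective N | Power, 55% vs 40% |
|---|---|---|
| 0 | 382.5 | 79.3% |
| 1% | 386.4 | 79.7% |
| 2% | 390.3 | 80.1% |
| 5% | 402.6 | 81.4% |
| 10% | 425.0 | 83.4% |

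To return to 85% the effective N must reach about 444, so R² must be about 1 − 382.5/444.2 = 13.9%.

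**5. Simulation check.** N = 383, 2,000 runs per cell (standard error of each power about 0.9 points), with 21 sites, blocks of 6 and 10% prior biological treatment assumed. The unadjusted rule was compared with a linear risk-difference model containing site, prior treatment and baseline VAS:

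| Prognostic effect | Unadjusted | Adjusted | Difference (points) |
|---|---|---|---|
| None | 78.8% | 78.0% | −0.8 |
| Weak | 80.0% | 80.9% | +0.9 |
| Moderate | 80.6% | 82.8% | +2.2 |
| Strong | 79.1% | 82.6% | +3.5 |

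Simulated type I error of the unadjusted rule at N = 383 was 0.0275, 0.025, 0.021 and 0.021 down these rows (standard error about 0.0035). It tends to be conservative only as the factors become prognostic. The adjusted model gave 0.026, 0.0275, 0.025 and 0.0285. Part of its apparent gain is therefore a return to the nominal level, and a replacement rule needs its own check.

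**The case against.** The strongest reply is that the plan is coherent. The trial is sized with an unadjusted two-proportion test and analysed with an unadjusted two-proportion rule, and that rule has the promised power at the planned N. This stands: there is no contradiction and no invalid inference.

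The gain may also be small. The endpoint is already a percentage of each participant's baseline, so what baseline VAS adds is uncertain. Sites are many and small, with about 128/21 ≈ 6 sham participants each. Biological treatment of the target disc within 12 months is an exclusion, so that stratum may be thin. This stands too, and is why the range starts at zero.

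Finally, the SAP is not shown and may hold an adjusted supporting analysis. That is fair for supporting and secondary models. It does not cover the primary calculation, because the article itself states the prior, the posterior quantity and the threshold.

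Four stronger readings are tempting, and the documents do not support them:
- A reader might infer that ignoring the strata inflates type I error. It does not.
- A reader might blame the unadjusted model for the fall from 85% to 79%. Roll-ins and loss to follow-up cause it, and it applies at +15 points; at +20 points, 255/128 still has 96.2% power.
- A reader might call the rule systematically conservative. That requires prognostic factors, and no section says that they are.
- A reader might say that the design balanced baseline VAS. It is not a stratification factor.

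**Conclusion.** The point holds as a modest efficiency concern. The primary analysis is fixed without the two randomisation factors and without a baseline measure held on every participant. It is valid, but less precise than it could be if these variables predict response. For 40% versus 55% at about 382 evaluable, the gain forgone is zero to about 4 points of power for R² from 0 to 10%.

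This rests on the assumed R², on all 21 roll-ins being used, on the 10% loss implied by Table 2, and on imputation recovering little of the information lost with missing participants. Adjustment would recover only part of the shortfall from 85% unless R² reached about 14%. The shortfall itself is a sample-size matter. The change is worth making because it needs no new data and leaves the estimand and decision rule unchanged, not because the planned analysis is unsound.

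**What to change.** Before any unblinded analysis, including the first interim look:

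- Make the primary model a Bayesian logistic regression with treatment, prior biological treatment (Y/N), continuous baseline VAS and a site random intercept, under stated weakly informative priors. A random intercept avoids fitting up to 21 × 2 = 42 stratum effects.
- Standardise over the analysed participants to obtain the marginal pT − pC, and apply the same 0.975 threshold.
- Keep the unadjusted beta-Jeffreys result as a supporting analysis.
- Add site, prior biological treatment and baseline VAS to the imputation model in {20c}.

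The cost is revised wording, extra programming and a simulation of type I error and power. That simulation must cover the interim looks and the multiple imputation as well as the final analysis, because the design is adaptive and a closed-form calculation is being replaced. If that cannot be finished in time, the minimum is to pre-specify the adjusted model as a sensitivity analysis and extend the imputation model.
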